**
[figure not shown]
**

**PROTOCOL SIGNATURE PAGE**

Assessing the Effectiveness of Different Interventions in Increasing the Completion Rates of the Advanced Medical Directive in the Polyclinic Setting in Singapore

Sponsor Name: N/A

Declaration of Investigator

I confirm that I have read and approved the above-mentioned protocol and its attachments. I agree to conduct the described trial in compliance with all stipulations of the protocol, regulations and Singapore Guideline for Good Clinical Practice (SGGCP).

| Principal Investigator Name:  _________Dr [name]_________________    Principal Investigator Signature:  _______________________________________    Date:  ________15/10/2017___________ |
| --- |

| **BACKGROUND AND RATIONALE** |  |
| --- | --- |
| An Advanced Medical Directive (AMD) is a legal document in Singapore that allows one to inform their medical practitioner that they do not want any life-sustaining treatment should they become unconscious and terminally ill where death is imminent. It may be completed by any person, of sound mind, aged 21 years and above. The AMD Act was passed in the Singapore Parliament in May 1996.  A cross-sectional, community-based study surveyed 1200 selected households in Singapore. Only **37.9%** of the sample population had heard of the AMD prior to the study, though when approached, **60.6%** were willing to sign an AMD^1^. As of 2017, less than 25,000 people (0.45%) in Singapore have opted to sign an AMD^2^.  Past studies have shown that end of life discussions reduce stress, anxiety, and depression in surviving relatives^3^. A local study in 2010 revealed a 33% patient-surrogate discrepancy in end-of-life decision making^4^.  There is a lack of intervention studies regarding AMD in Singapore. In recent years, the AMD has been the subject of much public discussion and debate, in light of Singapore’s ageing population, end-of-life planning and other related issues^1^.  In this study, we aim to compare the effectiveness of counselling sessions together with pamphlets, versus pamphlets alone, versus current care, in increasing the completion rates of the AMD in the Singapore Polyclinic setting. |  |
| **HYPOTHESIS AND OBJECTIVES** |  |
| We hypothesize that:   - Counselling with pamphlets will be more effective than pamphlets alone in increasing the uptake of the AMD. - Either intervention will increase the uptake of the AMD as compared to current care.   Primary outcomes:   - Number of patients who completed the AMD - Number of patient who expressed interest to complete the AMD   Secondary outcomes:   - Barriers to completion of AMD | |
| **EXPECTED RISKS AND BENEFITS** |  |
| This is a questionnaire-based study, no major risks are identified.  A lack of awareness is a frequently report reason for not completing an advance directive. In a study done by Tay et al in 2010, awareness of AMD in Singapore was 37.9%, though 60.6% among participants were willing to sign an AMD. Moreover, it was noted that high knowledge scores of the AMD of participants were associated with a greater willingness to complete an AMD.  While several intervention studies have shown that education and communication can be effective in promoting end-of-life discussion and planning, no such studies have been done in the primary care setting in Singapore.  We hope that through this study, we will be able to determine the most effective method in increasing the completion rates of the AMD in Singapore, thereby reducing stress, anxiety, and depression in surviving relatives. |  |
| **STUDY POPULATION** |  |
| List the number and nature of subjects to be enrolled. |  |
| 195 patients attending the Residency Continuity Clinic from January 2017 to May 2018 who fit the eligibility criteria will be enrolled and randomised into 3 arms: the active intervention group, the passive intervention group, and the control group. |  |
| Criteria for Recruitment and Recruitment Process |  |
| Informed consent will be obtained before initiation of the study. Potential participants will be approached during the Residency Continuity Clinic. Consent will be taken during clinic consultation in the consultation rooms. |  |
| Inclusion Criteria |  |
| - Age > 40 - Singhealth Polyclinics (Bedok, Marine Parade, Outram, Tampines) |  |
| Exclusion Criteria |  |
| - History of dementia - History of depression - Known diagnosis of terminal illness - Previously signed AMD or Advanced Care Planning |  |
| **STUDY DESIGN AND PROCEDURES/METHODOLOGY** |  |
| **Patient Enrolment:**  This is a randomised control trial consisting of 3 arms:-   1. **Active Intervention group (n=65)**    - Counselling provided    - Pamphlet given 2. **Passive Intervention group (n=65)**    - Pamphlet given 3. **Control group (n=65)**    - Neither counselling nor pamphlet given     **Randomization:**  Randomisation will be performed via block randomisation (total N=195) via Sequential Numbered Opaque Sealed Envelopes (SNOSE), in variable blocks of 6 and 9 (ratio of groups 1:1:1).    **Follow-up Assessment**  Post-intervention surveys will be conducted via telephone at 6 weeks by a blinded assessor.    A flowchart of the protocol is given in **Appendix 1**. |  |
| **SAFETY MEASUREMENTS** |  |
| Definitions |  |
| An adverse event (AE) is any untoward medical occurrence in a participant or clinical investigation subject administered a pharmaceutical product and which does not necessarily have a causal relationship with this treatment.  A serious adverse event (SAE) or reaction is any untoward medical occurrence that at any dose:   - Results in death - Is life-threatening - Requires inpatient hospitalisation or prolongation of existing hospitalisation - Results in persistent or significant disability/incapacity or - Is a congenital anomaly/birth defect - Is a medical event that may jeopardize the participant and may require medical or surgical intervention to prevent one of the outcomes listed above.   As this is a questionnaire-based study, no AEs or SAEs are expected. |  |
| Collecting, Recording and Reporting of Adverse Events and Serious Adverse Events to CIRB |  |
| Reporting of adverse events involves the PI submitting to the approving CIRB the completed SAE Reporting Form within the stipulated timeframe. PI is responsible for informing the institution representative (local SAE resulting in death), sponsor or regulatory bodies as required and appropriate.  Reporting timeline to CIRB:   - SAE that result in death, regardless of causality, should be reported immediately - within 24 hours of the PI becoming aware of the event. - Local life-threatening (unexpected/ expected) SAE should be reported no later than 7 calendar days after the Investigator is aware of the event, followed by a complete report within 8 additional calendar days. - Local unexpected SAE that are related events, but not life-threatening, should be reported no later than 15 calendar days after the investigator is aware of the event. - An increase in the rate of occurrence of local expected SAE, which is judged to be clinically important, should be reported within 15 calendar days after the PI is aware of the event. - Local expected SAE should be reported annually (together with Study Status Report for annual review). - Local unexpected and unlikely related SAE that are not life-threatening should also be reported annually (together with Study Status Report for annual review). - Local unexpected AE that are related events should be reported at least annually (together with Study Status Report for annual review). - Non-local unexpected SAE that are fatal or life threatening and definitely/probably/possibly related should be reported not later than 30 calendar days after the PI is aware of the event. |  |
| Safety Monitoring Plan N/A |  |
| Complaint Handling |  |
| Complaints will be handled by the research team and if required the Quality Assurance team at Singhealth. |  |
| **DATA ANALYSIS** |  |
| Data Quality Assurance |  |
| The Investigator(s)/ Singhealth will permit study-related monitoring audits, MCRC and or EC review and regulatory inspection(s), providing direct access to source data/ document. |  |
| Data Entry and Storage |  |
| Data will be stored in a private database in a stand-alone PC in each recruitment site's office under lock and key access. The principal investigator and co-investigators will have access to the data. This access can be monitored through the computer records. The data also will be coded and the participants will be de-identified and the master list will be locked with the password. De-identified data will also be stored in shared folders that can be accessed only by the research team members. |  |
| **SAMPLE SIZE AND STATISTICAL METHODS** |  |
| Determination of Sample Size |  |
| 156 patients are required to have an 80% chance of detecting as significant at the 5% level, an increase in the primary outcome measure from 2.3% in the control group to 18.6% in the experimental group^7^. The sample size calculation with adjustment made for 20% drop out rate is calculated to be 195^8^. |  |
| Statistical and Analytical Plans |  |
| - To assess primary outcomes of the number of patients who completed the AMD and the number who expressed interest to complete the AMD, Chi Square analysis or Fisher exact (categorical variables) will be used. - To assess secondary outcomes of barriers to completion of the AMD, descriptive anlysis will be used. |  |
| **DIRECT ACCESS TO SOURCE DATA/DOCUMENTS** The investigator(s)/institution(s) will permit study-related monitoring, audits and/or IRB review and regulatory inspection(s), providing direct access to source data/document. **QUALITY CONTROL AND QUALITY ASSURANCE** N/A **ETHICAL CONSIDERATIONS** This study will be conducted in accordance with the ethical principles that have their origin in the Declaration of Helsinki and that are consistent with the Singapore Good Clinical Practice and the applicable regulatory requirements.  This final study protocol, including the final version of the Participant Information and Informed Consent Form, must be approved in writing by the Centralised Institutional Review Board (CIRB), prior to enrolment of any participant into the study.  The principle investigator is responsible for informing the CIRB of any amendments to the protocol or other study-related documents, as per local requirement. |  |
| Informed ConsentConsent will be taken by the research team members after explaining the study protocol, obtaining voluntary agreement of the participant, explaining the number of visits and alternatives and after the participant is clear of his/her study rights. |  |
|  |  |
| Confidentiality of Data and Participant Records |  |
| Research data and participant database will be stored each recruitment site's office under lock and key access. Hard copies will be stored in Singhealth research office at Connection One, in a locked cabinet. |  |
|  |  |
| **PUBLICATIONS** |  |
| Please refer to the Singhealth publication policy. |  |
| **RETENTION OF TRIAL DOCUMENTS** |  |
| The research data will be stored for at least 15 years and then destroyed/deleted. |  |

| **FUNDING and INSURANCE** |
| --- |
| No funding was received for this study. |

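### Both block sizes are printed in the protocol of an open-label trial that does not separate recruiters from past allocations, so a few allocations could be known in advance

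*Protocol*

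**What the plan says.** Under Study Design and Procedures, the protocol states: "Randomisation will be performed via block randomisation (total N=195"), carried out "via Sequential Numbered Opaque Sealed Envelopes (SNOSE"), "in variable blocks of 6 and 9 (ratio of groups 1:1:1"). Each arm has 65 patients.

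The same section defines the arms as counselling plus pamphlet, pamphlet alone, and a control arm with "Neither counselling nor pamphlet given". Whoever delivers care therefore knows the arm. The only blinded role described is at follow-up: "Post-intervention surveys will be conducted via telephone at 6 weeks by a blinded assessor".

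On recruitment, the Study Population section says: "Consent will be taken during clinic consultation in the consultation rooms". The Informed Consent section assigns this task to research team members, who first explain the study protocol. The investigator's declaration reads: "I confirm that I have read and approved the above-mentioned protocol and its attachments". Four sites are listed: "Singhealth Polyclinics (Bedok, Marine Parade, Outram, Tampines").

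The available text does not say who prepares, holds or opens the envelopes, who gives the counselling or pamphlet, whether recruiters learn earlier allocations, or whether there is one list or one per polyclinic. The Appendix 1 flowchart is not reproduced in the text at hand, so its silence on the order of steps cannot be held against the plan.

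**The concern.** Opaque sealed envelopes stop a recruiter from reading the next allocation. They do not stop inference from earlier ones. In an open-label trial with balanced blocks, someone who has followed the list can work out which arms are still owed. Knowing the possible block sizes also tells that person when a guess is safe, and sometimes when it is certain.

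The outcomes here are completing the directive and expressing interest in it. A clinician may sense receptiveness before offering consent. On the planning rates, 65 patients give about 65 × 0.023 = 1.5 completers in the control arm and 65 × 0.186 = 12.1 in an experimental arm, so steering a few patients could move the contrast. A blinded telephone assessor cannot undo selection at entry.

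**Working it through.** **The plan's own figures.** With unpooled variance, two-sided 5% and 80% power, the size per arm is n = (1.96 + 0.84)² × [0.023 × 0.977 + 0.186 × 0.814] / (0.186 − 0.023)² = 51.4, so 52. Three arms give 156, and 156 / 0.80 = 195. Blocks of 6 and 9 can fill 195 exactly, for example 13 × 6 + 13 × 9 = 78 + 117 = 195. The scheme is arithmetically sound, and the sample size does not depend on it.

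**Inputs.** From the Randomization text: block sizes 6 and 9, ratio 1:1:1, total 195. From the inclusion criteria: four polyclinics, so equal site lists would hold 195 / 4 ≈ 49 patients.

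**Assumptions, not in the protocol.** Each block size has probability 1/2. The guesser knows the two sizes but not their order, sees every earlier allocation on one list, and picks the arm with the highest posterior probability. For a block with k places per arm, of which c are already used in arm a, P(next = a) = (k − c) / (places left in the block). This is averaged over the block states still possible.

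**Simulated results, blocks of 6 and 9, whole list seen:**

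| List length | Best guess correct | Certain | Over 60% probable |
|---|---|---|---|
| 49 | 53.6% | about 5% | 32% |
| 65 | 53.7% | about 5% | 32% |
| 195 | 54.2% | about 5% | 34% |

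Chance is 33.3%. In about 14% of allocations at least one arm is ruled out.

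**What disclosure adds.** A second guesser knows no block sizes and simply names the arm allocated least often so far. On the same lists this guesser scores the same 53.6% to 54.2%. The reason is structural: completed blocks are balanced, so differences in the running totals equal those within the current block, and the arm used least is always the most probable next, whatever the block size. Disclosure therefore does not raise the best-guess rate. It adds the roughly 5% of certain allocations and the ability to recognise which guesses are strong.

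**What varying the size still protects.** A known fixed block of 6 gives 20% certain and 56% correct. A known fixed block of 9 gives 14% certain and 53% correct. Mixing the two cuts certainty to about 5% even when both sizes are known.

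**Part of the list seen.** If the recruiter sees a random fraction of earlier allocations (an assumed fraction) and names the arm seen least, the success rate on lists of 49 to 195 is about 36% to 38% when half are seen and about 35% to 36% when a quarter are seen.

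**Larger undisclosed blocks.** For an equal mix of 9, 12 and 15, even if the sizes later become known and the whole list is seen, the best guess is right about 50% of the time and under 2% of allocations are certain.

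**The case against.** The strongest reply is that the protocol contains no error. It specifies sequentially numbered opaque envelopes and varying block sizes, and varying the size does protect: about 5% certain against 14% to 20% for a known fixed block. That stands. It would be wrong to say that varying sizes helps only when the sizes are secret.

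A reader might infer that the recruiting clinicians see each allocation and can guess upcoming arms before consent. The protocol does not say so. It documents that the principal investigator has read the protocol and that research team members take consent in clinic. It does not say that those people open envelopes, deliver the intervention or follow the whole sequence. With four polyclinics on a shared list, any one recruiter might see only part of it.

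A reader might also attribute the gap between 54% and 33% to the printed sizes. It does not come from them: the equal ratio and the seen allocations are enough, and the arm sizes of 65 each already reveal the ratio. Deleting the phrase would leave that gap in place.

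What survives is narrower. The sizes are disclosed in an open-label trial, no stated arrangement keeps recruiters from past allocations, and disclosure has a real though small effect on certainty and confidence.

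**Conclusion.** The point holds as a minor weakness of design. In the worst case, disclosure makes about 5% of allocations certain, or about 0.05 × 195 ≈ 10 patients, and lets a recruiter recognise the roughly one third that are predictable with over 60% probability. The 54% best-guess rate belongs to small balanced blocks together with seen allocations, and it falls towards 33% as less of the list is seen.

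These figures assume the two sizes are equally likely, one list, and every earlier allocation known to the recruiter. The protocol neither confirms nor excludes the last two conditions, so the actual risk lies somewhere between no advantage and the worst case. The documents do not show that selection bias has occurred or will occur.

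**What to change.** Replace the phrase giving the sizes with wording such as: *permuted blocks of randomly varying size; sizes held in a restricted file by a person not involved in recruitment*. State who prepares, holds and opens the envelopes, that the envelope is opened only after consent, and whether there is one list or one per polyclinic. As far as staffing allows, keep those who recruit from a running record of allocations; this, with larger blocks, is what lowers the best-guess rate.

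Generate the list with undisclosed and preferably larger sizes. The mix of 9, 12 and 15 only illustrates the gain, and the sizes actually used should not be published. The stated enrolment window opens in January 2017 and the declaration is dated October 2017, so recruitment may already have begun. In that case only the unused part of the list can be regenerated.

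The cost is a short amendment, a new list and new envelopes. Balance is slightly looser if recruitment stops mid-block: two arms can differ by at most 15 / 3 = 5 patients in a block of 15, against 9 / 3 = 3 in a block of 9. The figures of 156 and 195 are unchanged.

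### AMD completion is collected only by a 6-week telephone survey with no described check, and with about 1 versus 10 events expected, a few arm-dependent false reports could make a non-significant result significant

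*Protocol*

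**What the plan says.** Under Hypothesis and Objectives, the first of two primary outcomes is "Number of patients who completed the AMD"; the second is expressed interest in completing one. The Background describes the AMD as a legal document and cites a registry for the national count of signatories.

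Under Study Design and Procedures, Follow-up Assessment, the outcome collection is: "Post-intervention surveys will be conducted via telephone at 6 weeks by a blinded assessor". No other source of outcome data appears in the text. Expected Risks and Benefits describes the trial in the same way: "This is a questionnaire-based study, no major risks are identified". The registry is not named as a source of trial outcomes, and Quality Control and Quality Assurance is marked not applicable.

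Blinding is claimed for the assessor only. Participants consent after the study has been explained to them (Informed Consent). They then receive counselling plus a pamphlet, a pamphlet alone, or, in the control arm, "Neither counselling nor pamphlet given".

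Determination of Sample Size plans for "an increase in the primary outcome measure from 2.3% in the control group to 18.6% in the experimental group". Statistical and Analytical Plans names chi-square or Fisher's exact test.

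**The concern.** Signing an AMD is a concrete act that can in principle be checked, but the text describes only asking about it by telephone. When the participant is the source of the outcome, blinding the caller guards against a biased question or a biased recording. It does not guard against a biased answer. Someone counselled in person about the AMD knows it, and may be readier than a control to say that the form is done, or to count an intention or a half-completed form as completion. Such error would push the comparison towards the intervention.

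The planned number of events is small, so a handful of such answers could settle significance. The trial might then report that counselling raised completion when part of what it raised was the claim of completion.

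This cannot be left to a later analysis plan: details not asked for during the call cannot be recovered at analysis.

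**Working it through.** **Inputs.** From Determination of Sample Size: 2.3% and 18.6%, 5% significance, 80% power, 156 evaluable, 20% dropout, 195 enrolled. From Study Design: three arms, 1:1:1, 65 each. Sidedness is not stated; two-sided reproduces the plan's figure. The protocol does not say which of its two primary outcomes the rates describe. They are read here as completion rates.

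**Plan's own figure.** Unpooled two-proportion formula:

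n = (1.96 + 0.8416)² × [0.023 × 0.977 + 0.186 × 0.814] / (0.186 − 0.023)² = 7.849 × (0.02247 + 0.15140) / 0.026569 = 51.4, so 52 per arm.

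3 × 52 = 156, and 156 / 0.8 = 195, or 65 per arm. Both stated figures reproduce.

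**Expected events.** 52 × 0.023 = 1.2 in control; 52 × 0.186 = 9.7 in an experimental arm.

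**How many reports matter.** Two-sided p-values, 52 per arm, one control event:

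| Control v experimental | Fisher | Chi-square, uncorrected |
|---|---|---|
| 1 v 1 | 1.000 | 1.000 |
| 1 v 4 | 0.363 | 0.169 |
| 1 v 5 | 0.205 | 0.093 |
| 1 v 6 | 0.112 | 0.0504 |
| 1 v 7 | 0.060 | 0.027 |
| 1 v 8 | 0.031 | 0.015 |
| 1 v 10 | 0.008 | 0.004 |

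- Fisher reaches significance at 8 experimental events. Three false reports on a true 1 v 5, 1 v 6 or 1 v 7 therefore cross the line.
- Chi-square reaches it at 7. Three false reports take 1 v 4 (0.169) to 1 v 7 (0.027).
- From 1 v 1, three false reports give only 1 v 4, which is not significant by either test. Chi-square needs six (7 − 1) and Fisher seven (8 − 1).

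**False-positive probability under assumed over-reporting.** Assume true completion is 2.3% in both arms and a fraction r of counselled non-completers say yes, with none in control. The reported rate in the counselled arm is 0.023 + 0.977 × r. Summing over two independent binomials (n = 52 each), two-sided 5% test:

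| r | Expected false reports (52 × 0.977 × r) | Chi-square | Fisher |
|---|---|---|---|
| 0 | 0 | 1.9% | 0.07% |
| 2% | 1.0 | 6.0% | 0.7% |
| 5% | 2.5 | 19% | 6% |
| 10% | 5.1 | 50% | 31% |
| 15% | 7.6 | 77% | 62% |

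If controls also over-report, at 5% against 10% in the counselled arm, the reported rates are 0.023 + 0.977 × 0.05 = 7.2% and 0.023 + 0.977 × 0.10 = 12.1%. The probability falls to 13% (chi-square) or 6% (Fisher).

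**Cost of a stricter definition.** If 20% of true completers cannot supply details, the rates become 0.8 × 2.3% = 1.84% and 0.8 × 18.6% = 14.88%. Exact power with 52 per arm falls from 0.84 to 0.72 (chi-square) or from 0.71 to 0.55 (Fisher).

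**The case against.** **Nothing in the documents shows that over-reporting will occur.** No over-reporting rate is given, so every value of r is an assumption. Claiming to have signed a legal form is less open to a courtesy answer than expressing interest in one. At r = 2% with Fisher the inflation is negligible, and equal over-reporting in all arms would not favour counselling. This stands: the false-positive figures show what would follow from a given rate and are not a forecast.

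**A reader might infer that three false reports can create an effect where none exists.** The table does not support that. From 1 v 1, three reports give p = 0.36 (Fisher) or 0.17 (chi-square). Three suffice only when the true split already leans towards the intervention but falls short of significance.

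**A reader might also infer that removing three reports from the planned 1 v 10 always overturns it.** That holds for Fisher (1 v 7, p = 0.060) but not for uncorrected chi-square (p = 0.027), and the protocol allows either. The smallest expected count at 1 v 7 is 4, which makes Fisher the natural choice, but the plan does not fix it.

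**The absence of a check is inferred from silence.** The survey wording is not in the protocol and the Appendix 1 flowchart is not shown. The script may already ask for details, so it would go too far to say that the plan counts a bare yes. What can be said is that the text describes no check.

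**The remedy is still mostly self-report.** Date and witness come from the same participant, and counselled participants may know better what to answer. This also stands. Confirming questions filter mistaken or courtesy answers; only a record or a copy of the form verifies.

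**Conclusion.** The point holds as a cheap improvement to the design. A primary outcome that could be checked is collected, as far as the text shows, only by asking participants who know their arm, and blinding the assessor does not address that. With 1.2 versus 9.7 expected events, three false reports can move a non-significant result across the 5% line, while six or seven are needed to do so from equality.

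The size of the threat depends on an unknown over-reporting rate. Between 2% and 15%, in counselled participants only, the chance of a spurious significant result runs from 6% to 77% by uncorrected chi-square and from 0.7% to 62% by Fisher. It is much smaller if controls over-report too. These figures rest on 52 analysed per arm, on reading 2.3% and 18.6% as completion rates, and on equal true completion of 2.3%.

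The documents do not support the conclusion that the result will be biased. They support the narrower one that, as described, the plan could not tell a rise in completion from a rise in reported completion.

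**What to change.** In Follow-up Assessment:

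- Define completion as a signed AMD.
- Ask each participant who says yes, in the same call, for the signing date, the witness and whether the form was submitted.
- Check against a clinic record or a copy of the form where one is available.
- Classify each case without knowledge of arm.
- Report both detail-supported completion and plain self-report, and claim increased completion only if the two agree.

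The cost is a few extra questions for about 21 expected responders at the plan's rates (1.2 + 9.7 + 9.7 = 20.6, taking 18.6% in both intervention arms). That is an expected count, not a maximum. Some true completers may be missed, with the loss of power shown above if 20% are. That loss bears on the claim, since both definitions must agree, but reporting both keeps the self-reported rate visible. The change reduces reliance on self-report without removing it.

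### Two unranked primary outcomes and three implied contrasts share one bare test and a sample size built for a single contrast at 5%

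*Protocol*

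**What the plan says.** Under Hypothesis and Objectives the protocol expects counselling with pamphlets to do better than pamphlets alone, and states that "Either intervention will increase the uptake of the AMD as compared to current care". Read naturally, that is three contrasts: active vs passive, active vs control and passive vs control. The same section names two primary outcomes, the number completing the AMD and the number expressing interest in doing so. Neither is put first, and no rule says whether one or both must succeed.

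Under Study Design: "This is a randomised control trial consisting of 3 arms", with 65 patients in each.

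Under Determination of Sample Size: "156 patients are required to have an 80% chance of detecting as significant at the 5% level", for "an increase in the primary outcome measure from 2.3% in the control group to 18.6% in the experimental group". The "adjustment made for 20% drop out rate is calculated to be 195".

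Under Statistical and Analytical Plans, for both primary outcomes: "Chi Square analysis or Fisher exact (categorical variables) will be used". Nothing says whether this means one test across three arms or tests between pairs, in what order, or how the 5% is shared. No multiplicity rule appears elsewhere in the protocol.

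**The concern.** The hypotheses, the analysis and the sample size do not fit together. The hypotheses ask which arm beats which. The analysis names a test that, over three arms, may not answer that. The sample size gives the whole 5% to one comparison on one outcome.

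As written, the outcome, the comparison and the choice between chi-square and Fisher could all be settled after the data are seen, with any p below 0.05 reported as a primary result. The protocol hopes to identify the most effective method, so this bears on its main conclusion.

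**Working it through.** **Inputs from the protocol.** 5% level and 80% power; 2.3% vs 18.6%; 20% drop-out; three arms, 1:1:1; two primary outcomes; a 60.6% willingness to sign, from the background section. **Assumptions.** Two-sided testing (sidedness is not stated, but two-sided reproduces N); null completion of 2.3% or 5-15%; null interest of 30% or 60.6%; pamphlet-arm completion of 8-13%.

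**1. The protocol's own figure.** Unpooled two-proportion formula, per arm:

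n = (1.960 + 0.842)² × [0.023 × 0.977 + 0.186 × 0.814] / (0.186 − 0.023)²
= 7.85 × 0.1739 / 0.02657 = 51.4, so 52.

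52 × 3 = 156, and 156 / 0.8 = 195. Both figures reproduce exactly. N therefore rests on one contrast at an unadjusted 5%.

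**2. One three-arm test per outcome** (simulated, 52 per arm, completion given as active/passive/control):
- 18.6/18.6/2.3%, where active equals passive: rejects about 83% of the time.
- 18.6/2.3/2.3%, where passive equals control: rejects about 89% of the time.

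The test is nearly as likely to be significant in one case as in the other, so a significant result does not say which hypothesis is true. Two such tests at 5% on independent outcomes give 1 − 0.95² = 9.75%; simulation gives about 9-10%.

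**3. Six unadjusted pairwise tests.** Three contrasts that share arms give a familywise error of 12.2% on one outcome under normal theory. Over two independent outcomes this is 1 − (1 − 0.122)² = 22.9%. Treating all six as independent, 1 − 0.95⁶ = 26.5%, is too high because the contrasts share arms.

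Simulation with binomial data at 52 per arm, no true differences and independent outcomes:

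| Test | Null completion | At least one false positive in six |
|---|---|---|
| Chi-square | 5-15% | 22-24% |
| Chi-square | 2.3% | 17-18% |
| Fisher when expected counts are below 5, else chi-square | 2.3% | 13-14% |
| Fisher throughout | 2.3-15% | 7-15% |

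At 2.3% an arm of 52 expects 0.023 × 52 = 1.2 completions. The three completion contrasts then contribute only 0.2% (Fisher for small counts) to 4.8% (chi-square), and most of the inflation comes from the interest outcome.

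Correlation lowers the risk. Under normal theory the 22.9% becomes 22%, 21%, 20%, 17% and 12% at correlations of 0.3, 0.5, 0.7, 0.9 and 1.0.

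**4. A three-arm test gating the pairwise tests.** With three arms, any two true pairwise nulls imply the third. The gate therefore holds 5% within one outcome. Over two outcomes the total is about 5-10%.

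**5. What splitting alpha would cost at the present N** (same formula and rates):
- Alpha/3: 69 per arm, 207 evaluable, 259 with drop-out; power at 52 per arm about 66%.
- Alpha/6: 80 per arm, 240 evaluable, 300 with drop-out; power at 52 per arm about 57%.

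**The case against.** The strongest reply is that the order of contrasts and the allocation of alpha are commonly left to a statistical analysis plan, which may exist, and that the protocol nowhere says its tests will be unadjusted. This stands in part: a missing multiplicity paragraph alone would not be a finding. But the protocol itself fixes two co-listed primary outcomes and a sample size that spends all of the 5% on one contrast. A later split of alpha would lose the stated 80% power, as step 5 shows.

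Four stronger readings are tempting and not supported:

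- *The false-positive risk is about 23%, more than four times nominal.* That holds only for chi-square at completion rates above the planned 2.3%, with independent outcomes. The protocol also allows Fisher, and completion and interest are probably positively related.
- *No contrasts are named.* The hypotheses name them in words. What is missing is their link to the tests. The phrase about either intervention could also mean both pooled against control, which is a further ambiguity.
- *No reading of the plan controls error.* A three-arm test followed by pairwise tests is a usual reading, and it does so within each outcome.
- *Any one of six wins counts as success.* The protocol states no success rule, and both hypotheses speak of uptake. Six tests is the widest family the text permits, not one it declares.

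**Conclusion.** The concern holds in a limited form. The protocol does not link its tests to its hypotheses, does not rank its primary outcomes, and is sized for one contrast on one outcome. With independent outcomes, the chance of at least one false primary finding is roughly 7-24% for six unadjusted pairwise tests, about 9-10% for two three-arm tests, and up to about 10% for gated pairwise tests on both outcomes. Correlation between outcomes reduces these figures. At the planned 2.3% completion rate the six-test figure is 17-18% with chi-square, 13-14% with Fisher for small counts and 7-9% with Fisher throughout. These figures assume 52 evaluable per arm and no true differences.

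This should be fixed. It does not invalidate the design, because the powered contrast can keep its full 5% and the remedy leaves N unchanged.

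**What to change.** Name AMD completion as the single primary outcome, since it is the natural match to uptake in the hypotheses, and make interest secondary. Then fix the order of testing:

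1. Active vs control on completion, two-sided 5%.
2. Only if step 1 is significant: active vs passive and passive vs control on completion, each at two-sided 5%.

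This controls familywise error strongly. If active and control are truly equal, any false claim first needs a false rejection at step 1. If they differ, at most one of the remaining nulls can be true, because both together would make active equal control. State which test is used and when, and report risk differences with 95% confidence intervals for every contrast, whether or not the gate opens.

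Costs. Interest loses its primary status, which is an amendment to be notified to the CIRB. Step 2 is not confirmatory if step 1 fails. Step 2 also has low power: with chi-square, 52 per arm and pamphlet completion of 8-13%, about 11-34% for active vs passive and 23-51% for passive vs control. The protocol should say so, because active vs passive is its first hypothesis.
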